### Blinding

It is not possible to blind the participants to group allocation for psychological interventions; however, the study purpose will be masked to participants. The study statistician will also be blinded to the group allocation. Participants’ personal identifiers will not be included in the dataset.

### Intervention

Participants in the experimental group will receive the GMPMI. A new participant (a pregnant woman in her second trimester) is expected to complete the eight EBMI lessons in eight weeks and practice mindfulness for about 30–60 minutes daily. The eight-session mindfulness-based intervention is developed from the Mindfulness-Based Cognitive Behaviour (MBCT) protocol for pregnant women. It integrated four-immeasurable meditation, including loving-kindness, compassion, appreciative joy, and equanimity meditations. Different themes are introduced to the participants weekly during the intervention period. These themes include ‘deepening capacity for present’, ‘connecting with breath and body’, ‘inner inspection’, ‘raise awareness of your thoughts’, and ‘savouring goodness’. Prompts and guidance for daily mindfulness practice will be sent to each participant through a social media platform. Participants will also be asked to keep a log of their daily mindfulness practice from T0 to T3 using Google Form. An assisting therapist will be available for online support and will initiate a chat every week throughout the intervention period. The chats will focus on participants’ experiences of or difficulties in the mindfulness practice. The assisting therapist will be supervised by an experienced mental health practitioner and a mindfulness teacher.

### Control condition

To control for attention and placebo effects, each new participant in the control group will receive a weekly web-based psychoeducation program for perinatal care (WPPP). WPPP is the parallel program this study adopted for the control group. In this program, essential perinatal and postnatal care knowledge are provided to the participants. Neither mindfulness elements nor counseling support will be given. An assisting therapist will also be available for online support and will initiate a chat every week throughout the intervention period. The chats will focus on participants’ experiences of the psychoeducation program.

### Measures

The outcome measures of the study are summarized in Table 1, including the detailed time-points at which the measures will be taken. In order to fulfill the study objective, the primary outcome variables include a battery of scales to measure MPS, mindfulness, positive appraisal and HRV. Secondary outcome variables include more general measures of psychological and physical wellbeing. Anxiety is considered as a more general measure which could be influenced by life events other than pregnancy, and is thus included as a secondary measure. To investigate the impact of the intervention on children, clinical obstetric and neonatal outcomes will also be collected. Other individual data such as demographic data and social support levels will be measured. All the questionnaire links will be sent to the participants through WhatsApp at each time-point for them to fill in on their own devices.

**Table 1 pone.0270683.t001:** Outcome variables.

Variables	Measures	Timepoints
**Primary outcome variables**		
Maternal psychological stress		
General stress	Perceived Stress Scale –10 items–The scale measures subjective perception of stress with two subscales, perceived helplessness and perceived self-efficacy [36, 37].	T0, T1, T2, T3,
Pregnancy- specific stress	Prenatal Distress Questionnaire– 12 items–The scale consists of three factors–concerns about birth and baby, weight and body image, emotions and relationships [38].	T0, T1, T2
Depression	Edinburgh Postnatal Depression Scale–Chinese– 10 items–The scale has been validated in the Chinese population with satisfactory psychometric properties [39].	T0, T1, T2, T3
Mindfulness		
State mindfulness	Short-form Five Facet Mindfulness Questionnaire– 20 items–The scale consists of five subscales–observing, describing, acting awareness, non-judging of inner experience and non-reacting to inner experience [40].	T0, T1, T2, T3
Daily mindfulness	Daily Mindful Responding Scale– 4 items–A measure designed to assess mindful responding in the daily lives of people undergoing mindfulness training [41].	Every week until T3
Positive appraisal		
Coping	Prenatal Coping Inventory– 22 items–consists of four subscales–preparation, avoidance, positive appraisal and prayer [42].	T0, T1, T2
Heart rate variability		
HRV Index	CorSense by Elite HRV–A merchandise device monitoring heart rate variability	T0, T1, T2, T3
**Secondary outcome variables**		
Psychological wellbeing		
Anxiety	Short-form State subscale of the State-Trait Anxiety Inventory– 6 items—The scale has been validated in pregnant women with satisfactory psychometric properties [43].	T0, T1, T2, T3,
Affect	Positive & Negative Affect Subscales of Body-Mind-Spirit Wellbeing Inventory– 8 and 16 items—The two subscales measure common positive and negative affect in Chinese adults [44].	T0, T1, T2, T3,
Spirituality	Chinese Daily Spiritual Experience Scale– 16 items–The scale measures a person’s perception of transcendence involvement in daily life [45, 46].	T0, T1, T2, T3,
Physical wellbeing		
Stagnation	Stagnation Scale– 16 items—The scale measures a cluster of mind and body obstruction-like symptoms depicted in Chinese medicine. It has three factors: body/mind obstruction, affect/posture inhibition, and overattachment [47, 48]. Stagnation was identified as a mediator in explaining the mechanism of change in mindfulness [49].	T0, T1, T2, T3,
**Clinical outcomes**		
Obstetric outcomes	Gestational age at birth, pregnancy complications, mode of birth.	T3
Neonatal outcomes	Birth weight, head circumference, months of maturity, Apgar score.	T3
**Individual factors**		
Socio-demographic	Age, gender, marital status, family income, employment, education, gestational age, parity, obstetric history, medical history, pre-pregnancy BMI.	T0
Social support	Prenatal Social Support– 4 items–The scale measures the level of social support women receive during pregnancy [50].	T0, T1, T2

HRV index will be collected through CorSense device. This device is designed as a finger clip which is portable and easy for the pregnant women to use. HRV scores will be calculated automatically. The higher HRV score indicates a better mental health status. The calculation of HRV score is based on the components of the HRV measurements. The R-R intervals will be captured through the Corsense monitor, followed by an industry standard RMSSD calculation. After applying a natural log (ln) to RMSSD, HRV score is conceptualized with a magnitude ranging from 0 to 100. In the meantime, the Corsense device can also capture the raw data of standard deviation of NN intervals (SSDN), the root mean square of the successive difference (rMSSD) in R-R intervals, and low frequency (LF), high frequency (HF), and very low frequency (VLF). This can serve as complementary data for the research team to do data analysis. Elite HRV provides a Team Dashboard for the research team to manage the participants’ data in a more convenient way. All the HRV scores and raw data will be sent to the Team Dashboard once the participant completed the measurement.

### Safety considerations

To our knowledge, there are no safety issues for pregnant women in practicing mindfulness or receiving maternal and neonatal care education. A safety exercise review will be provided for participants during the intake interview and will include the local GP contact, project staff contact and suggestions of a safe place to practice. The participants will be encouraged to report any adverse events occurring during practice as soon as possible by WhatsApp. We also have an experienced obstetrics and gynaecology specialist to provide advice to the participants as required to ensure their safety. Any adverse events will be reported by the principal investigator to the Human Research Ethics Committee at the University of Hong Kong using an adverse event report.

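### Adverse-event reporting is invited only for events during practice, which only the intervention arm does, so solicited reports are not comparable between arms and do not match the plan's own onward-reporting sentence

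*Protocol article*

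**What the plan says.** Safety considerations describes how adverse events reach the team: "The participants will be encouraged to report any adverse events occurring during practice as soon as possible by WhatsApp". It opens with a statement of prior knowledge, "To our knowledge, there are no safety issues for pregnant women in practicing mindfulness or receiving maternal and neonatal care education", and ends with onward reporting: "Any adverse events will be reported by the principal investigator to the Human Research Ethics Committee at the University of Hong Kong". The onward sentence is limited neither to practice nor to one arm.

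The Intervention section asks women in the mindfulness arm to "practice mindfulness for about 30–60 minutes daily". The Control condition section says of the psychoeducation arm: "Neither mindfulness elements nor counseling support will be given". That arm does have regular contact: "An assisting therapist will also be available for online support and will initiate a chat every week throughout the intervention period".

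Table 1 lists outcomes that bear on harm. Perceived stress, depression, anxiety and affect are measured from T0 to T3. At T3 the plan collects obstetric data ("Gestational age at birth, pregnancy complications, mode of birth") and neonatal data ("Birth weight, head circumference, months of maturity, Apgar score"). The ethics section says that both groups complete the listed questionnaires.

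**The concern.** What prompts a report is an exposure that the design gives to one arm. A woman in the control arm who follows the instruction literally has nothing to report, whatever happens to her. A woman in the intervention arm is asked only about the part of the day when she practises. Counts gathered this way reflect the reporting rule as well as the frequency of events.

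Two uses of these reports are at stake. First, the ethics committee is promised any adverse event, but the investigator can pass on only what is received. Second, no data monitoring committee was formed, on the grounds of timeframe and minimal known risk, and the team says it will keep that decision under review. Adverse-event reports are an obvious input to that review. The Discussion also expects the programme to be promoted to clinics and public hospitals, where a harms record that can be compared with the control arm would be wanted.

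**Working it through.** The plan states no adverse-event rate, safety margin or safety power, so there is no figure to reproduce. The check sets the sections side by side.

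**1. Scope of intake against scope of onward reporting (both in Safety considerations).** Intake covers events during practice. Onward reporting covers any event. The second is wider than the first, and no other solicitation is described that would fill the difference.

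**2. What the intake rule covers in each arm, under three readings of the word practice.**

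| Reading | Intervention arm | Control arm |
|---|---|---|
| Mindfulness practice (literal) | Events in the daily 30–60 minutes | Nothing |
| Taking part in one's own programme (loose) | Events in the daily 30–60 minutes and in lessons | Events while using weekly educational material |
| Any event during the study | All events | All events |

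Only the third reading gives equal coverage and agrees with the onward-reporting sentence. Under it, the words limiting reports to practice do no work. Under the other two, the arms have different windows and events outside those windows are not solicited in either arm.

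**3. Size of the window in the intervention arm (literal reading).** A day has 24 × 60 = 1,440 minutes.
- 30 / 1,440 = 0.0208, or 2.1%
- 60 / 1,440 = 0.0417, or 4.2%

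An event unrelated to practice and equally likely at any time of day would fall inside the window about 2% to 4% of the time. Events provoked by practice but emerging later would also fall outside it.

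**4. Whether other planned data fill the gap.**
- Weekly chats: both arms have them, but as described they deal with experience of the programme (practice and its difficulties in one arm, the educational material in the other), not adverse events. They run during the intervention period, whereas follow-up goes on to five weeks postpartum.
- Stress, depression, anxiety and affect scales: the same in both arms, T0 to T3. They would pick up sustained worsening of mood, but not a transient episode between time-points or a non-psychological event.
- Obstetric and neonatal outcomes at T3: no restriction by arm. They cover pregnancy and birth, not general or psychological events.

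The gap is therefore partly filled. What remains is adverse-event reporting as such.

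**The case against.** The best case for the plan is that the rule is loosely worded and not meant to restrict. The sentence is addressed to all participants, the next step covers any adverse event, an obstetric specialist is available to participants as required, and both arms have weekly contact. Harm-relevant scales and clinical outcomes are collected in both arms. The article is also a condensed account, so adverse-event definitions and forms may stand in a fuller document.

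Much of this stands. The absence of forms or definitions is not a finding; the point rests only on a restriction that the article states. If the wording is merely loose, correcting it costs almost nothing.

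Four stronger readings are tempting, and the documents do not support them:
- A reader might infer that harms are captured in one arm only. The mood scales and the obstetric and neonatal outcomes are collected in both.
- A reader might infer that the trial cannot test its claim of safety. That statement reports prior knowledge; it is not among the four hypotheses, and the outcomes shared by both arms allow a partial look at harm.
- A reader might infer that the WhatsApp channel itself favours one arm. The Measures section sends questionnaire links to all participants by WhatsApp.
- A reader might assume an event rate and count all intervention-arm events against none in the control arm. No rate is given, and the rule also misses intervention-arm events outside practice. The article's Data analysis section plans no between-arm comparison of adverse events in which a false excess would be declared.

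**Conclusion.** The point holds in a limited form. As written, solicited adverse-event reports differ by arm by design, omit events outside practice sessions in both arms, and fall short of the scope promised to the ethics committee. The one size that the documents support is the 2.1% to 4.2% of the day covered by the literal rule in the intervention arm. It assumes practice at the stated daily length and, as a capture rate, applies only to events unrelated to practice. The number of events lost cannot be estimated.

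The conclusion assumes that staff and participants follow the sentence as it stands; if both arms in fact report everything, only the wording is at fault. Primary and secondary efficacy analyses are unaffected. Severity is minor to moderate.

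**What to change.** 1. In Safety considerations, delete the words that limit reports to practice, so that solicitation has the same scope as the onward-reporting sentence.
2. Add one identical adverse-event question for both arms to the T1, T2 and T3 questionnaires, which already go to participants by WhatsApp. Use the same recall period in both arms, for example since the previous questionnaire, and ask about any event whether or not it seems linked to the programme. Keep the invitation to report promptly between questionnaires.
3. Tabulate the answers by arm, with spontaneous reports shown separately from those given in answer to the question.

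The cost is one item in each of three existing questionnaires, one table, and some unrelated events to record and report. Treatment, sample size and efficacy analysis do not change.

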### Ethical consideration and declarations

This trial was approved by the Human Research Ethics Committee of the University of Hong Kong (HREC Reference No.: EA1812034). Participants assigned to the intervention group will be voluntarily participate in the current trial. Participants assigned to the control group will receive the psychoeducation program (treatment as usual). Online written informed consent will be provided to the participants in both intervention and control groups after being informed in writing about the study. Participants from both intervention and control groups will fill out questionnaires as listed in the measure part of the article.

### Data analysis

Quantitative data including scale measures and the HRV index will be collected at four time-points as articulated above.

Intention-to-treat analysis will be performed and missing data due to drop–out will be handled by the ‘multiple imputation’ technique [51]. 1) Using a two-arm RCT design, the efficacy of the intervention will be examined by repeated measures MANOVA on both the primary and secondary outcome variables, while adjusting for individual factors. Partial eta-squared values will be calculated to measure the effect size; values of .02, .13 and .26 suggest small, medium, and large effect sizes, respectively [52]. 2) To investigate the within-group effect, serial trend analysis from T0 to T3 will be conducted on the primary and secondary outcome variables. 3) A series of linear mixed-effects models will be fitted to assess the mediation effects. 4) The software Elite HRV Team Dashboard will be used for HRV data collection. Three HRV indexes will be computed for analysis, namely RMSSD (Mean squared difference between consecutive normal-to-normal intervals), SDNN (standard deviation of beat-to-beat intervals) and HF (absolute power of HF band).

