**Method:**

This study is a randomized controlled trial that follows a parallel design. Consenting pregnant women in their second trimester (between 12^th^ and 20^th^ week gestation) will be randomly assigned to an intervention group (GMBPMI) or a control group (psychoeducation). The intended sample size is 198, with 99 participants in each group. Three levels of outcomes will be measured at baseline, post intervention in both the intervention and control groups, and at 36-week gestation and five-week postpartum. The primary outcomes include maternal psychological stress, mindfulness and positive appraisal HRV. Secondary outcomes are psychological and physical wellbeing. Tertiary outcomes include obstetric and neonatal outcomes, and social support. Analyses will follow an intention-to-treat method and repeated measures MANOVA will be conducted to compare changes in primary and secondary outcomes. A series of mixed-effects models will be fitted to assess the mediation effects.

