In recent decades, empirical research has suggested the efficacy of MBI in reducing MPS. For example, a meta-analysis of 17 studies of prenatal MBI demonstrated significant pre- and post-improvements of medium effect size in reducing stress and depression [20, 21]. However, there were no significant postnatal improvements in stress and depression or in mindfulness skills for MBI participants versus the control participants [20]. Lau and colleagues [22] suggest a need to implement the intervention in the second trimester and extend the intervention to the third trimester and postnatal to prevent postpartum depression. MBI was also found to be associated with enhanced biological and infant outcomes. Higher maternal mindfulness of women at 22-week gestation significantly predicted a normal, as opposed to low, neonatal birth weight [23]. Van den Heuvel and colleagues [24, 25] showed that maternal mindfulness was negatively correlated with maternal anxiety during pregnancy, and positively associated with fewer infant self-regulation problems, a less difficult temperament, and greater control in infants at ten months old. In a randomized controlled trial examining the efficacy of MBI among pregnant women, Chan [26, 27] found mothers in the MBI group to have lower levels of the “stress hormone” salivary cortisol in the evening, and the infants at five months old had easier temperaments as well as improved positive appraisal. However, the significant effects were only observed among the 56% of participants who practiced mindfulness regularly [28]. Lack of continued motivation was the most common reason reported for giving up the practice, suggesting a need to extend the current MBI from the second trimester of pregnancy to the third trimester and postnatal period.

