### Four hypotheses

The intervention group would show a greater increase in maternal mindfulness and positive appraisal than the control group at T1, T2 and T3.The intervention group would show a greater reduction in stress and depression than the control group at T1, T2 and T3 and these outcomes would be mediated by the enhancement in positive appraisal.The intervention group would show a greater increase in HRV than the control group at T1, T2 and T3 and these outcomes would be mediated by the reduction in stress and depression.The levels of stress and depression would be negatively associated with obstetric and neonatal outcomes at T3 and these correlations would be mediated by HRV.

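### Hypotheses 1 to 3 claim a benefit at T1, T2 and T3, but the only between-arm efficacy test is an omnibus repeated measures MANOVA, from which a benefit at T3 cannot be concluded

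*Protocol article*

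**What the plan says.** The section Four hypotheses makes three between-arm claims, each with a direction and each naming three visits:

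- Hypothesis 1: "The intervention group would show a greater increase in maternal mindfulness and positive appraisal than the control group at T1, T2 and T3".
- Hypothesis 2: "The intervention group would show a greater reduction in stress and depression than the control group at T1, T2 and T3".
- Hypothesis 3: "The intervention group would show a greater increase in HRV than the control group at T1, T2 and T3".

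The Data analysis section assigns efficacy to one procedure: "the efficacy of the intervention will be examined by repeated measures MANOVA on both the primary and secondary outcome variables". It does not say which MANOVA effect is meant. The abstract comes closest: "repeated measures MANOVA will be conducted to compare changes in primary and secondary outcomes".

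The other listed analyses do not compare the arms visit by visit. The trend analysis is within arm: "To investigate the within-group effect, serial trend analysis from T0 to T3 will be conducted on the primary and secondary outcome variables". The linear mixed models are for mediation. Partial eta-squared, the stated effect size, has no sign and refers to no visit.

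In Table 1, perceived stress, depression, five-facet mindfulness and the HRV index are scheduled at T0 to T3. The prenatal distress and coping scales are scheduled at T0, T1 and T2 only, and positive appraisal is a subscale of the coping scale.

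**The concern.** The abstract's reference to changes, and the hypotheses' wording in terms of greater increase or reduction, point to the group-by-time effect. Its null hypothesis is that the change from T0 is the same in both arms at every visit. Rejection says that some contrast of the visits differs, in some direction. The hypotheses say more: the arms differ at each of three visits, in the stated direction.

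T3 is the visit where this matters most. The Introduction reports from a meta-analysis of prenatal mindfulness interventions that "there were no significant postnatal improvements in stress and depression or in mindfulness skills for MBI participants versus the control participants", and it argues for extending the intervention into the postnatal period. A benefit before birth that has gone by T3 is therefore an outcome the plan must be able to tell apart from a lasting one, and the named test cannot do so.

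There is also a cost when the hypothesis is true. The group-by-time test spreads a constant post-baseline benefit over three degrees of freedom and so loses power.

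**Working it through.** **Inputs from the protocol article.** Four visits (Design). From Sample size calculation: effect size 0.4 (read here as a standardised mean difference d), alpha .008, 99 per arm and 25% attrition. After attrition, 99 × 0.75 ≈ 74 per arm.

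**Assumptions.** One outcome measured at all four visits, unit SD, no arm difference at T0, and exchangeable correlation ρ = .5, with .3 and .7 as the range. The protocol gives no correlation.

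**The plan's own figure.** The 99 per arm can be neither confirmed nor refuted, because the correlation, number of measurements and test family are not stated. With four measurements and ρ = .5, the between-factors formula gives 123 per arm (164 with attrition) and the interaction formula 33 (44). The points below do not depend on which was used.

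**Group-by-time test.** This is Hotelling's T² on the three changes from T0, with F on 3 and 2n − 4 df. Under exchangeable correlation the noncentrality is

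λ = (n/2) × [Σd² − (Σd)²/4] / (1 − ρ),

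where d is the arm difference at each visit and d = 0 at T0. At n = 99, ρ = .5:

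| Effect at T1, T2, T3 | Bracket | λ | Rejects |
|---|---|---|---|
| .4, .4, .4 (lasting) | .48 − .36 = .12 | 49.5 × .12/.5 = 11.88 | 60.0% |
| .4, .4, 0 (gone at T3) | .32 − .16 = .16 | 15.84 | 77.5% |
| .4, 0, 0 (T1 only) | .16 − .04 = .12 | 11.88 | 60.0% |
| .4, .2, 0 (steady fade) | .20 − .09 = .11 | 10.89 | 54.6% |

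At n = 74, λ is 8.88 for lasting (42.1%) and 11.84 for gone at T3 (59.1%). Simulation with 20,000 trials per cell agrees: 59.2% and 77.7% at 99 per arm, 42.2% and 58.9% at 74. For ρ from .3 to .7 at 99 per arm, the lasting effect gives 40.3% to 88.6% and the effect gone at T3 gives 56.9% to 96.9%.

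**Group main effect, the other possible reading.** λ = (n/2) × d̄² / [(1 + 3ρ)/4], with d̄ the mean over four visits.

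- Lasting: 49.5 × .09/.625 = 7.13, rejects 49.8%.
- Gone at T3: 49.5 × .04/.625 = 3.17, rejects 18.7%.

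The order reverses, but a rejection still does not identify T3.

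**Baseline-adjusted average over T1 to T3.** After adjustment for T0, each visit has variance 1 − ρ² and each pair of visits has covariance ρ − ρ². The mean of three visits has variance [(1 − ρ²) + 2(ρ − ρ²)]/3 = (.75 + .50)/3 = .4167. The standard error of the arm difference is √(2 × .4167/n): .0917 at n = 99 and .1061 at n = 74. The two-sided .008 critical value is 2.652 (normal approximation).

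- Lasting, n = 99: .4/.0917 = 4.36, power Φ(1.71) = 96%.
- Lasting, n = 74: .4/.1061 = 3.77, power Φ(1.12) = 87%.
- Gone at T3, n = 99: mean effect .8/3 = .267; .267/.0917 = 2.91, rejects Φ(0.25) ≈ 60%.

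The average is thus a good overall test, but it does not show a T3 effect either.

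**Single-visit contrast.** The standard error is √(2 × .75/n): .1231 at n = 99 and .1424 at n = 74. Power at d = 0.4 is Φ(3.25 − 2.652) ≈ 73% and Φ(2.81 − 2.652) ≈ 56%.

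**All three visits in sequence, each at .008, lasting effect.** Power at 99 and 74 per arm is about 46% and 26% at ρ = .5, 30% and 15% at .3, and 77% and 55% at .7. If the effect is gone at T3, all three contrasts pass in only about 0.3% of trials (ρ = .5, 99 per arm).

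**The case against.** **The ordering is not general.** A reader might infer from 77% against 60% that the MANOVA rewards an effect that vanishes after birth over one that lasts. The documents do not support that as a general statement. It holds for the profile (.4, .4, 0) under the group-by-time effect. A T1-only effect is rejected as often as a lasting one, a steady fade less often, and under a group main effect the order reverses. The protocol does not name the effect. This objection stands, and the ordering is used here only as an illustration.

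**No decision rule is stated.** A reader might also infer that the trial will report a T3 benefit whenever the MANOVA rejects. Nothing in the protocol says that rejection counts as support at every visit. Visit contrasts and the rule for using them may sit in an analysis plan that is not shown, and their absence from an article would be no finding. What remains is narrower: the article states both the hypotheses and the efficacy test, and that test does not answer those hypotheses. A better-matched test is also more powerful for a lasting effect.

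**The vanishing effect is a scenario.** The cited null postnatal result concerns prenatal programmes, whereas this trial aims to extend support past birth and logs practice up to T3. That is fair: the result makes the scenario plausible, but does not make it the expected one. The first aim, on distress over the perinatal period, can be addressed by an overall test. The visit-specific hypotheses cannot.

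**Conclusion.** The point holds in this form: the only named between-arm efficacy analysis cannot support claims about T1, T2 and T3 separately, and a T3 benefit in particular cannot be concluded from it. This is true whichever MANOVA effect is tested.

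For a lasting effect of d = 0.4, the group-by-time test has 60% power at 99 per arm and 42% at 74, against 96% and 87% for the baseline-adjusted average. These figures assume one outcome measured at all four visits, exchangeable correlation .5 and alpha .008. They apply to perceived stress, depression, five-facet mindfulness and HRV.

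For positive appraisal the problem is more basic: hypothesis 1 claims a benefit at T3, and Table 1 schedules no T3 measurement of it, so no analysis can test that part.

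The analysis should be changed before the data are analysed. The design need not be.

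**What to change.** 1. For each outcome, replace the omnibus MANOVA with a longitudinal model of the post-baseline visits, adjusted for the T0 value, with arm, visit and arm-by-visit terms. The planned multiple imputation and adjustment for individual factors can stay.
2. Make the baseline-adjusted arm difference averaged over the post-baseline visits the overall efficacy test, at the corrected alpha.
3. Report the between-arm difference at each visit with its confidence interval. After the averaged test, take the visit contrasts in the fixed order T1, T2, T3 at the same alpha. Claim benefit at a visit, T3 above all, only if that visit's own contrast passes in the hypothesised direction.
4. For the prenatal distress and coping scales, use T1 and T2 only. Drop or restate the T3 claim for positive appraisal in hypothesis 1.

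The cost is analysis wording, with no new data. The downside should be stated openly: a claim at all three visits becomes hard to reach, with about 46% power at 99 per arm and 26% at 74 (30% and 15% at correlation .3; 77% and 55% at .7). For the two-visit scales the averaged test is somewhat weaker. At correlation .5 the variance is (.75 + .25)/2 = .50 and the standard error is √(2 × .50/n) = .1005 or .1162, which gives about 91% power at 99 per arm and 78% at 74.
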